### **12. Recruitment of participants and informed consent**

In connection with the initial planning of surgical treatment in the outpatient clinics, the project nurses will screen patients referring to the inclusion and exclusion criteria. For patients meeting the inclusion criteria and none of the exclusion criteria, a project nurse will approach the patient and offer more information about the project. If they are interested in hearing more about the project, they are contacted by the local project team. Before this meeting, the patient is informed that family members and/or other important persons are welcomed on invitation of the patient. Interested patients will have oral and written information about the study and an invitation to participate. The patient information follows the guidelines from the National Committee on Health Research Ethics.

During the meeting, the oral and written participant information is given by the project members, and there is time for questions and answers. The dialogue takes place in a private and neutral room close to the out-patient clinic. Relatives or another relevant person ('bisidder') are invited to participate – depending on the patients' wishes. The patients take the time necessary for consideration in the hospital or at home, normally up to a few days.

## STRONG – Hernia, Version 5 (12-05-2024)

All participants are included after informed consent and can withdraw their consent without further explanation and without influence on the treatment and care in the department. Patients, who withdraw the informed consent or say no thank you to participate in the randomised trial are asked about a separate informed consent for being followed-up via the medical records and the health registries.

The informed consent is collected timely to allow for 4-6 weeks prehabilitation with the STRONG program. If the operation is postponed, the prehabilitation period is extended until surgery (e.g., 8-

|                                              | 2023 | 2024 | 2025 | 2026 |
|----------------------------------------------|------|------|------|------|
| Protocol article writing                     | X    |      |      |      |
| Study 1-A Inclusion & data collection | X    | X    | X    |      |
| Analysing +Article writing                   | X    | X    |      |      |
| Study 1-B Data collection             | X    | X    | X    | X    |
| Analysing + Article writing                  |      | X    | X    | X    |
| Study 2 Data collection               |      | X    | X    | X    |
| Analysing + Article writing                  |      |      | X    | X    |
| Study 3 Data collection               |      | X    | X    | X    |
| Analysing + Article writing                  |      |      |      | X    |
| Study 4-A Analysing + Article writing |      |      | X    |      |
| Study 4-B Analysing + Article writing |      |      |      | X    |
| Study 4-C Analysing + Article writing |      | X    |      |      |
| Study 4-D Analysing + Article writing |      | X    |      |      |
| Running information of the project           | X    | X    | X    | X    |

12 weeks). They are also welcomed to use the project hotline in case of further questions and considerations. Participants are included only after informed consent and would then be randomized to either the intervention or control group.

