## 2. Objectives

### 2a) Problem description, hypotheses, outcomes, and the rationale

Despite the great developments taking place during and after surgery, e.g., intraoperative techniques and enhanced recovery after surgery (the ERAS protocol), there is a large untapped potential for risk reduction in the preoperative period via effective lifestyle intervention targeting one or more co-existing risky lifestyles: Smoking, malNutrition, obesity, risky Alcohol intake and insufficient Physical activity (SNAP).

The STRONG project is national multicentre research with international impact. The overall goal is to obtain the potential extra health gain from the individually tailored, combined and intensive lifestyle intervention – STRONG - in relation to surgery, thereby adding to lower the inequity in health. As SNAP factors are frequent and have a negative social gradient, they strike hardest among disadvantaged patients, thereby developing most postoperative complications. In this project we would be able to reach out to surgical patients, who have not been reachable otherwise.

This clinical research benefits from mixed methods and comprehends several sub-studies:

1. Efficacy of the 6-week preoperative STRONG-program compared to treatment as usual (TAU) on (RCT):
  - A. risky lifestyles, preoperatively and complications, 1-month postoperatively
  - B. risky lifestyles and complications at 3 and 6-month follow-up
2. Efficacy of STRONG compared to TAU on health gain after 6 months and 2-year follow-up
3. Cost-effectiveness of the STRONG program on short and longer term (for 1. A+B and 2.)
4. Prevalence of SNAP factors in the potential study population and the potential for risk reduction.
5. Secondary analyses (Cohort analyses):
  - A. Dose-response of SNAP factor improvement (number/type) and complications as well as predictors for complication-free hernia repair
  - B. Dose-response of SNAP factor improvement (number/type) and health on long-term as well as predictors for improved health
  - C. Associations between self-reported and validated lifestyles
  - D. Associations between patient reflections of motivation, priority, self-efficacy, and lifestyle changes (Nested Qualitative analysis to the intervention group)

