### The hypotheses

The primary hypothesis is that STRONG halves the postoperative complications within 1 month compared to the daily routines.

Secondly, improvement of postoperative complications after 3 and 6 months, risky SNAP lifestyles, health, and the cost-effectiveness as well as improvement of health and costs after 2 years.

In addition, we hypothesise associations

- between preoperative patient reflections and successful change of SNAP factors
- as a dose-response of SNAP factor improvement and complications, as well as predictors for complication-free hernia repair
- as a dose-response of SNAP factor improvement and health gain, as well as predictors for a health gain
- between self-reported and validated SNAP factors.

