### Analyses

Analyses are done blinded as Intention-to-Treat (ITT). We will use Fisher's exact test for frequencies, Mann-Whitney for continuant variables, and  $p < 0.05$  is chosen for statistical significance. To benefit future meta-analyses, we will also give the parametric results. This would also meet the tradition that costs are usually reported with means and standard error (SE), mean difference (MD), and 95% confidence interval (CI). Bootstrapping procedures are used to calculate the cost-effectiveness plane and the acceptability curve by repeatedly resampling the data (1,000 incremental cost and effect pairs). Sensitivity analyses will be performed for differences in local standards for the control groups among the surgical centres. Analyses as per-protocol, dose-response, prediction, sensitivity, and the other secondary analyses are done by logistic regression models including control for confounders and effect-modifiers and reported as Risk Rates with 95% Confidence Interval (CI). The results are considered significant if the CI does not involve 1.00.

Absolute (ARR) is calculated as the events in the control group minus the events in the intervention group, and the relative risk reduction as the ARR divided by the events in the control group. The number needed to treat was calculated by  $1/ARR$ . We will present the mortality as Kaplan-Meier plots and test by the log rank test.

In case of dropouts, the primary outcome is collected from the medical record and a telephone follow-up after acceptance from the patient. In case of missing health data, the lifestyle at baseline will be imputed as the results in order not to over-estimate the results of changing lifestyle. This would expectantly impact the results to a similar degree in both groups.

All quantitative analyses are performed in SPSS Statistics® version 22.

The qualitative analyses are done using Kirsti Malterud's approach of systematic text condensation.

After import into NVivo® qualitative data analysis software version 11, the systematic text condensation in the four steps takes place: 1) Total impression of all answers and identifying preliminary themes, 2) coding by identifying and sorting meaning units, 3) condensation into code groups, and 4) synthesising the condensates into a story grounded in the empirical data.

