### The control group

The control group receives the standard care regarding the SNAP factors. This includes the participant information, weight loss and smoking cessation initiatives, according to local routines, and access to support offered outside the project.

The project does not involve placebo intervention in the control group.

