### 6b) Discontinuation

Participant withdrawal: A participant may withdraw from the study at any time without this impacting on any future investigations and/or treatments at the site.

Individual participant discontinuation: The investigator may discontinue any participant's participation for any reason, including an adverse event, safety concerns or failure to comply with the protocol.

Discontinuation of entire study: The principal investigator has the right to terminate this study at any time. Reasons may include the following, but are not restricted to unsatisfactory fulfillment the design, participant enrolment, keeping the timeschedule, or agreement with the description in the application.

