### 13. Dissemination of results

All results will be published – positive, negative, or inconclusive, including in [www.clinicaltrials.gov](http://www.clinicaltrials.gov). The results will be disseminated for each sub-study after its finalisation. Authorships follow the Vancouver Criteria. Furthermore, the results will be spread to the public at the website, by lectures and through the participant's networks. The timeline is depicted in table 5.

Table 5. Overview of the timeline for the STRONG-Hernia project.

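### Table 5 dates the analysis of Study 1-A, the primary comparison, to 2023-2024 although inclusion runs through 2025, which contradicts the fixed 2 x 199 design and release after finalisation

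*Protocol*

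**What the plan says.** Table 5 (grid printed in section 12, caption in section 13, Version 5) gives the timeline by calendar year. For Study 1-A, "Inclusion & data collection" is marked 2023, 2024 and 2025. The next row, "Analysing +Article writing", is marked 2023 and 2024, and is blank for 2025 and 2026.

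Section 2a defines Study 1-A as the randomised comparison of STRONG with usual treatment on "risky lifestyles, preoperatively and complications, 1-month postoperatively". The primary hypothesis is that "STRONG halves the postoperative complications within 1 month compared to the daily routines". Study 1-A is therefore the primary comparison.

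Section 4 sizes the trial at 2 x 199 for 20% versus 10%, with 80% power and two-sided 0.05. No interim look or division of alpha is described. Section 13 states: "The results will be disseminated for each sub-study after its finalisation". That section also points to Table 5 for the timeline.

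**The concern.** Table 5 is the only place where the primary analysis is given a date. Read as printed, it has patients included in 2025 entering the trial after the only period in which Study 1-A is analysed and written up.

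Two things are at stake:

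- **Incomplete sample.** A primary test run on that schedule would have fewer patients than section 4 requires, and so less power than the protocol states.
- **Knowledge of results during recruitment.** Section 3a says of usual care: "The project does not involve placebo intervention in the control group". The protocol does not use the term open-label, but an intensive counselling programme set against local routine cannot be concealed from patients or from those who deliver it. Project nurses screen and approach patients (section 12), and project nurses provide the intervention (section 3c). If an arm difference became known before inclusion closed, it could influence who is approached and what the control group receives.

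**Working it through.** **1. Is this only the coarseness of a yearly grid?** The table's own rows can be compared:

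| Study | Inclusion / data collection | Analysis and writing |
|---|---|---|
| 1-A | 2023-2025 | 2023-2024 |
| 1-B | 2023-2026 | 2024-2026 |
| 2 | 2024-2026 | 2025-2026 |
| 3 | 2024-2026 | 2026 |

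For 1-B, 2 and 3 the analysis row reaches the last data-collection year. Only for 1-A does it stop before. Section 7 points the same way: the tobacco and alcohol markers are to be analysed mainly once all samples are in, so the validated-lifestyle part of Study 1-A could not largely be done in 2023-2024.

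**2. The protocol's sample size.** Inputs from section 4: p1 = 0.20, p2 = 0.10, two-sided 0.05, power 80%. With mean rate 0.15 and pooled variance, without continuity correction:

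n = [1.960 × √(2 × 0.15 × 0.85) + 0.842 × √(0.20 × 0.80 + 0.10 × 0.90)]² / 0.10²
= [1.960 × 0.505 + 0.842 × 0.500]² / 0.01 = 198.96, rounded up to **199 per arm**.

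The stated figure is reproduced, and it belongs to a single test on the full sample.

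**3. Sample available on the Table 5 dates.** Assumption: 400 patients accrue evenly over 2023-2025.
- End of 2023: 400 × 1/3 ≈ 133, or about 67 per arm.
- End of 2024: 400 × 2/3 ≈ 267, or about 133 per arm.

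This ignores the lag from consent through prehabilitation and surgery to the 1-month outcome, so the numbers with a known outcome would be lower.

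**4. Power for 20% versus 10% at those sizes.**
- Normal approximation: Φ{[0.10 × √n − 1.960 × 0.505] / 0.500}.
- Exact power of Fisher's test, which section 3a names for frequencies: the sum over all outcome pairs (a, b) of Bin(a; n, 0.20) × Bin(b; n, 0.10), counted where the Fisher p-value is below 0.05.

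| Per arm | Normal approximation | Exact Fisher |
|---|---|---|
| 67 | 36.6% | 28.7% |
| 100 (half accrual) | 50.8% | 44.4% |
| 133 | 62.8% | 57.3% |
| 199 | 80.0% | 76.6% |

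Like for like with Fisher's test, analysing at the end of 2024 costs 76.6 − 57.3 = 19.3 percentage points.

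**5. Type I error.** This matters only if an early unadjusted 0.05 test is followed by a final one. Fisher's test was simulated at a common rate of 15%, the mean of the two planning rates:

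| Looks | Fisher's test | Normal theory |
|---|---|---|
| End only | about 3.6% | 5% |
| 2/3 and end | about 5.5% | 7.7% |
| 1/3, 2/3 and end | about 7.2% | 10.7% |

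The Fisher column is the relevant one. Because that test is conservative, the excess over 5% is small.

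**The case against.** The strongest reply is that a year-level planning grid is not an analysis plan. No section provides for an interim look, and none gives arm results to recruiting staff. Sections 3a and 9a say analyses are performed blinded. A row that combines analysing with writing and starts in the first year of inclusion may cover preparation. The grid also looks outdated: it labels four sub-studies 4-A to 4-D where section 2a has a four-part set of secondary analyses labelled 5-A to 5-D. It ends in 2026, although two-year follow-up of a patient included in 2025 runs into 2027.

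Most of this stands. A reader might infer that the investigators intend to test the primary outcome during recruitment; the documents do not support that. The blinded-analysis statements do not, however, complete the sample, and coding the arms does not prevent an early comparison. Preparation is a possible reading, but the protocol article has its own row. An outdated table in the current version still needs correcting.

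A reader might also add low power from an early test to inflated error from repeated testing. These are alternatives. If nothing is analysed after 2024 there is one underpowered test; if a final test follows, the early power is no longer decisive.

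Finally, section 6b says "The principal investigator has the right to terminate this study at any time", and a reader might infer that early results could drive stopping. The reasons listed there are operational (design, enrolment, schedule, agreement with the application), although the list is not exhaustive. A general right to terminate is not evidence of stopping on results.

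**Conclusion.** The point holds as an internal contradiction. The only dates given for the primary analysis fall before inclusion ends, against a fixed 2 x 199 single-test design and release after finalisation. It is most likely an uncorrected timetable and not a planned early look, so the consequences are conditional on the table being followed.

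In that case exact Fisher power is about 57% at 133 per arm, against 76.6% at 199. This assumes even accrual and takes no account of follow-up lag, which would lower the first figure further. Arm results could become known during unblinded recruitment; the documents do not say that they would. Type I error is a secondary matter: about 5.5% or 7.2% with Fisher's test at a 15% common rate, and only if early testing is followed by a final test.

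**What to change.** - Move the Study 1-A analysis row in Table 5 to after the last randomised patient's 1-month postoperative visit. If inclusion runs to the end of 2025, that falls in 2026.
- Start between-arm analysis for Studies 1-B and 2, now marked from 2024 and 2025, only after their own last follow-up. Extend the table beyond 2026 where the two-year data require it.
- Align the table's study labels with section 2a, and re-date any row that uses complications by arm.
- Add one sentence to section 3a or 13: no outcome is compared by arm before the corresponding data are complete.

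If an early look is in fact wanted, it should instead be declared as an interim analysis, with control of alpha and restricted access to results by arm.

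The cost is an edit to the table and one sentence. The downside is that the first results paper appears later. The protocol article and other work that does not compare the arms can keep their dates.

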### 13. Dissemination of results

All results will be published – positive, negative, or inconclusive, including in [www.clinicaltrials.gov](http://www.clinicaltrials.gov). The results will be disseminated for each sub-study after its finalisation. Authorships follow the Vancouver Criteria. Furthermore, the results will be spread to the public at the website, by lectures and through the participant's networks. The timeline is depicted in table 5.

Table 5. Overview of the timeline for the STRONG-Hernia project.

### 14 Scientific Ethical Considerations

The risk of participation is very low or negligible, and we anticipate that the intervention group will benefit from participation. The control group will receive standard care. The inconvenience that sometimes follows a change of lifestyle is often short and efforts are taken for prevention. This project aims at halving the complication rate after surgery on short term and improve the health on longer term for future patients. However, patients in the intervention group may benefit from these possible effects already during the study period. All patients may feel positive by the extra examinations and measurements as well as the open access to the project staff during the project period. Overall, the low risk of participation seems to be well balanced by the benefits, thereby justifying running the project.

The project is covered by the usual patient insurance for all patients in public as well as for the possible future centres at private hospitals.

